#### 2.13.1. Questionnaire for Patients

Several questionnaires will be provided to patients to analyse the following:
Acceptability and usability
a.Technology Acceptance Model [69]: after 5 sessions, after 15 sessions, at T1;b.Ad hoc questionnaire for needs and available solutions and perception of their relative complexity: at T0 and T1;Satisfaction (ad hoc questionnaire): at T0 and T1;Confidence and knowledge of ICT technologies (ad hoc questionnaire): at T0;Costs (ad hoc questionnaire): at T0, after 15 sessions, at T1;Quality of life (EQ-5D-5L [62]): at T0, after 15 sessions, at T1.

The ad hoc questionnaires for patients are provided in Supplementary Materials S1.

#### 2.13.2. Questionnaires for Operators

In addition to the study and control groups, the group of healthcare professionals involved in rehabilitation will also be included in the analysis, and they will be asked to respond to questionnaires regarding the following:Confidence and knowledge of ICT technologies: at the beginning of the study;Quality of work (Work-Related Quality Of Life scale, [70]): at the beginning of the study, 6 months after, and 12 months after;Technology Acceptance Model [69]: at the beginning of the study, 6 months after, and 12 months after;Ad hoc questionnaire for needs and available solutions and perception of their relative complexity: at the beginning of the study, 6 months after, and 12 months after;Satisfaction (ad hoc questionnaire): at the beginning of the study, 6 months after, and 12 months after.

### 2.14. Patient’s Involvement in the Study Design

The study design was developed based on the needs identified through a survey conducted by the Fit4MedRob Consortium, targeting both patients and healthcare professionals. The survey revealed that many respondents experience simultaneous impairments across multiple functional domains, such as movement, posture and balance, upper limb function, cognitive abilities, self-care, and communication. Additionally, the survey highlighted economic concerns, with respondents indicating that treatments are only partially reimbursed by the National Health System, underscoring a significant financial burden on patients.

### 2.15. Sample Size

As previously reported [71,72], a change of 9.25 points in the 0–100 version of the modified Barthel Index corresponds to a change of 1.85 points on the 0-to-20-point version of the BI, which has been shown to be clinically significant [73]. Thus, an MCID (minimal clinically important difference) of the modified Barthel Index of 9.25 points can be considered.

The sample size was thus determined considering the following with respect to the primary outcome (the modified Barthel Index):The non-inferiority of robotic treatment compared to traditional treatment;A non-inferiority margin of 5 points (about half of the MCID);A statistical power of 80%;A bilateral 95% confidence interval;A standard deviation of the primary outcome of 20 points.

Considering these parameters, a sample size of 506 patients (253 per group) is obtained. Additionally, considering a dropout rate of 15%, a total sample size of 596 patients is obtained. The same sample size is sufficient to also demonstrate the potential superiority of robotic treatment. Considering a significance level of 5%, a statistical power of 80%, an MCID of 9.25 points, a standard deviation of 20 points, and a dropout rate of 15%, a total of 178 patients are required to demonstrate superiority.

All calculations were performed using the software G*Power v.3.1.9.7 [74].

### 2.16. Blinding

Given the nature of the study, neither patients nor clinical investigators can be blinded to the treatment; however, evaluations will be conducted by evaluators unaware of the treatment group, and similarly, data analysis will be conducted blindly.

### 2.17. Study Withdrawal

Participants have the freedom to withdraw from the study at any point and for any reason, providing notification to the principal investigator of the study. In this case, no further data concerning the patient will be collected, and he/she may request the deletion of the data already collected. Current and future medical care at the corresponding clinical centre will not be affected by patients’ decisions, and the physicians will continue to treat him/her with due attention. Additionally, investigators retain the authority to remove participants from the study if they believe it is no longer beneficial for them to participate, such as due to unforeseen illness or adverse events.

### 2.18. Statistical Analysis

The collected data will be presented using descriptive statistics such as mean and standard deviation for numerical variables and percentages for categorical variables. An Intention-To-Treat (ITT) population will be defined to include all patients randomised to the experimental group or the control group. A Per-Protocol (PP) population will be defined to exclude randomised patients who were not eligible at baseline (i.e., patients inappropriately randomised) and those who did not receive the full treatment (due to treatment interruption for any reason).

#### 2.18.1. Primary Analysis

The primary endpoint of the modified Barthel Index variation at the end of treatment will be compared between treatment groups using a mixed-effects linear model with the clinical centre as a random effect to obtain a corrected estimate of variance and, therefore, a correct confidence interval for the difference between the changes in the two groups. Non-inferiority will be assessed at a significance level of 2.5% by estimating the effect with a bilateral 95% confidence interval (CI) and comparing the lower limit of the CI with the non-inferiority margin of −5 points. For the analysis of the primary outcome, the mixed-effects model will initially be applied to the PP population. The analyses will be completed according to the Intention-To-Treat strategy [75,76], including all randomised subjects, along with a sensitivity analysis. The ITT population will be defined by assuming a follow-up, and therefore an evaluation of outcomes, on subjects who interrupt treatment. The analysis will be conducted assuming that missing data are “missing at random” (MAR); therefore, a mixed model for repeated measures will be applied, including all subjects in the analysis. With respect to the assumption of MAR, a sensitivity analysis will be performed considering scenarios deviating from it and involving one or both groups. Additionally, a sensitivity analysis will be used to assess additional adjustments for baseline modified Barthel Index values. If non-inferiority is concluded for the primary outcome, superiority can be evaluated without the need for correction for multiple comparisons. Regarding the primary outcome, an analysis of planned subgroups will be conducted to assess the presence of treatment effect modifiers, extending the models to include interaction terms between these factors and treatment.

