### 2.9. Specific Interventions

#### 2.9.1. Experimental Group: Integrated Treatment with Robotic and Technological Devices

The experimental intervention involves administering a rehabilitative treatment, as described above, using (also) RADTs. Based on the equipment available at each centre, different devices may be used; however, harmonisation of the treatments provided across all centres will be ensured by using, in each centre, devices that enable rehabilitation in the following domains:(A)Upper limb sensorimotor abilities;(B)Lower limb sensorimotor abilities and gait;(C)Balance;(D)Cognitive abilities.

To ensure a standardised treatment for patients enrolled in the different centres and randomised into the experimental group, a precise and punctual rotation of the four domains listed above has been adopted. The treatment plan dictates that, starting from the first day, patients will address domain A, followed by domain B on the second day, and so on, continuing with the A-B-C-D sequence until the completion of 25 total treatment sessions, as illustrated in Figure 2. This strict rotation ensures a consistent and balanced delivery of the intervention, always following the domain sequence to guarantee a standardised rehabilitation.

Specifically, for rehabilitating sensorimotor function of the upper limb (Domain A) in the proximal (shoulder), semi-distal (elbow), and distal (hand) regions, the following devices may be used:Planar end-effector robots for shoulder-elbow rehabilitation, or exoskeletons or electromechanical systems for shoulder, elbow, and wrist rehabilitation;End-effector robots or exoskeletons for the hand;Sensor-based devices for comprehensive upper limb treatment.

For rehabilitating sensorimotor function of the lower limb (Domain B), the following ones will be considered:End-effector robots or exoskeletons (overground and non-overground) for the lower limb;Treadmills with body-weight support systems.

Balance training under static and dynamic conditions (Domain C) will be ensured by the following:
Robotic and digital stabilometric platforms;Sensor-based systems.

For cognitive functions (Domain D), digital systems, sensor-based devices, and virtual reality programmes will be used to train memory, attention, visuospatial skills, and executive functions.

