The treatment will be conducted within a gym equipped with devices enabling treatment of all identified domains, following a predetermined rotation, as previously illustrated, where two physiotherapists will supervise a group of patients ranging from 4 to 6, depending on the severity of their clinical condition. In each robotic session, at least 100 repetitions are performed. All devices used in the study must already have a CE mark for medical devices and be used according to the manufacturer’s intended use.

Information on the experimental intervention with RADTs was reported following the Template for Intervention Description and Replication (TIDieR) Checklist [55].

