#### 2.9.2. Control Group: Traditional Treatment

In the control group, subjects will undergo a standard traditional rehabilitation programme without the use of RADTs, focusing on activities and objectives mentioned in the section “Interventions”, using traditional methods of physiotherapy and cognitive rehabilitation. As in usual clinical practice, a physiotherapist-to-patient ratio of 1:1 is provided for the treatment in all participating centres.

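### The centre random effect does not capture variation in outcome between RADT gym groups or between centres' RADT device sets and teams, so the claim of a correct non-inferiority interval holds only under unstated conditions

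*Protocol article*

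**What the plan says.** Randomisation is individual, 1:1 and stratified by centre (sections 2.2 and 2.7), so each centre contributes patients to both arms.

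Delivery differs by arm. In the RADT arm "two physiotherapists will supervise a group of patients ranging from 4 to 6" in a shared gym, and "Based on the equipment available at each centre, different devices may be used" (both section 2.9.1). In the control arm "a physiotherapist-to-patient ratio of 1:1 is provided for the treatment in all participating centres" (section 2.9.2). The Discussion names differing technologies across centres as a limitation and accepts that some heterogeneity cannot be avoided.

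The primary analysis (section 2.18.1) is a linear mixed model, specified "with the clinical centre as a random effect to obtain a corrected estimate of variance and, therefore, a correct confidence interval for the difference". No other clustering term is named. Non-inferiority is declared if the lower limit of the two-sided 95% interval lies above -5 points (one-sided 2.5%). Superiority may then be assessed without correction for multiplicity.

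In section 2.15, for a margin of 5, an SD of 20 and 80% power, "a sample size of 506 patients (253 per group) is obtained", or 596 with 15% dropout. No design effect enters.

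**The concern.** A random intercept for centre describes what both arms of a centre have in common. When both arms are present in each centre, that common part cancels from the within-centre difference between arms. Patients who share a gym group, a device set or a RADT team may have correlated outcomes, and this correlation does not cancel. If it exists and is not modelled, the standard error of the treatment difference is too small.

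In a non-inferiority comparison an interval that is too narrow lies further from the margin than it should, so the error favours declaring success. The superiority step inherits the same interval. The Introduction presents a lower therapist-to-patient ratio as a possible gain from RADT, so a false declaration would have practical consequences.

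**Working it through.** **Inputs.** From section 2.15: margin 5, SD 20, 253 analysed per arm, 15% dropout. From section 2.9.1: groups of 4 to 6. From section 2.5: at least 30 patients expected per site, hence at most 596/30 = 19.9, about 20 centres. With 20 centres, 253/20 = 12.65 RADT patients per centre are analysed. *Assumption:* RADT-arm ICC between 0.02 and 0.10, since the article gives none.

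**The plan's own figure.** The normal approximation gives n = 2 × 20² × (1.96 + 0.842)² / 5² = 251.2, so 252 per arm. The noncentral t distribution gives 253, so 506 in total, and 506/0.85 = 595.3, so 596. Power with 253 per arm is Φ(5/(20 × √(2/253)) − 1.96) = Φ(5/1.778 − 1.96) = 80.3%. The stated size reproduces, for independent patients.

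**Why the centre intercept does not help.** Write the outcome as mean + centre effect u + (RADT arm only) treatment effect θ + centre-specific deviation v + gym-group deviation g + residual. In the difference between arms within a centre, u cancels, while v and g remain. The planned model estimates u and the residual only.

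**Size by formula.** With m RADT patients per cluster, the design effect is DE = 1 + (m − 1) × ICC in the RADT arm. The standard error (SE) is multiplied by r = √((1 + DE)/2). Power with a correct SE is Φ(5/(1.778 r) − 1.96). The one-sided error of the uncorrected interval is Φ(−1.96/r).

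| Cluster | ICC | DE | r | Power | One-sided error |
|---|---|---|---|---|---|
| Gym group, m = 5 | 0.05 | 1.20 | 1.049 | 76.5% | 3.1% |
| Centre, m = 12.65 | 0.02 | 1.233 | 1.057 | 75.8% | 3.2% |
| Centre, m = 12.65 | 0.05 | 1.583 | 1.136 | 69.7% | 4.2% |
| Centre, m = 12.65 | 0.10 | 2.165 | 1.258 | 60.8% | 6.0% |

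**Check by simulation.** Setup: 20 centres, 13 patients per arm per centre, SD 20, true difference −5, centre effects redrawn in each of 8,000 runs, and the planned analysis represented by its balanced within-centre form.

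- No RADT clustering: error 2.5%, coverage of the 95% interval 95.0%.
- Centre-level ICC 0.05: model SE 1.70 against a true SE of 1.96, coverage 91.2%, error 4.5%.
- Centre-level ICC 0.10: model SE 1.69 against 2.20, coverage 86.9%, error 6.5%.
- Gym groups of 4 to 5, ICC 0.05: coverage 93.8%, error 3.2%.

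The model SE hardly moves (1.71 to 1.69) as the centre-level ICC rises, so the shared intercept does not pick up this variance. Across simulations with 17 to 20 centres, the error at centre-level ICCs of 0.02, 0.05 and 0.10 is about 3.3%, 4.5% and 6.6%. This is slightly above the formula because the model's own residual variance shrinks as the ICC rises.

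**What the assumed ICC means.** A centre-level ICC of 0.05 implies that the RADT effect varies between centres with SD √0.05 × 20 = 4.5 points. At 0.02 it is 2.8 points, and at 0.10 it is 6.3.

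**The case against.** **The inference target.** The simulations redraw centre effects, so they address a wider population of centres. If the centre effects are held fixed and the target is the average effect in the participating centres, the planned model's error stays at 2.4% to 2.6% for centre-level ICCs from 0 to 0.10 (17 and 20 centres, balanced). This stands. A reader might infer that the 2.5% level and the 80% power simply fail, but the documents do not support that. The centre-level part depends on the target, although treating centre as random and defending varied devices on grounds of generalisability (Discussion) point to the wider one. Limiting inference to the participating centres does not remove the gym-group part.

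**The size of the ICC.** At 0.05 the between-centre SD nearly equals the margin. The fixed rotation of domains, the minimum number of repetitions and the equal number of sessions all limit such variation. This stands as a reason to show a range. If the ICC is zero, nothing is wrong.

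**Clustering only in the RADT arm.** A reader might infer a dedicated RADT team in each centre and no clustering among controls. Section 2.10 says only that a patient's RADT therapists differ from those who treat the same patient traditionally. The one-to-one control ratio applies to a session, and a control therapist may treat several patients. Fixed membership of gym groups is not stated either.

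**Left to the statistical analysis plan.** Variance structures often are. Here, however, the article names the clustering term and asserts that it makes the interval correct. The treatment interactions planned in sections 2.18.1 and 2.18.2 are separate analyses and leave the primary interval unchanged.

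**Conclusion.** The point holds in a limited form. The statement in section 2.18.1 that the centre effect gives a correct interval is true only without RADT-specific clustering or, for the centre-level part, only for inference limited to the participating centres. Neither condition is stated. For any positive ICC outside those conditions, the error is towards declaring non-inferiority.

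The effect is small if only gym groups matter and moderate if RADT effects vary between centres regarded as random; the figures are in the working. They rest on an assumed ICC and on about 17 to 20 centres, inferred from the expected recruitment per site.

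A stronger reading, that the primary model must be replaced, is not supported. That is a choice of inference target on which statisticians may differ.

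**What to change.** In section 2.18.1, drop the statement that the centre effect alone gives a correct interval. Pre-specify a sensitivity analysis of the non-inferiority conclusion, reported beside the primary result. It adds a random treatment-by-centre effect (or a centre effect acting only in the RADT arm), with Satterthwaite or Kenward-Roger degrees of freedom. Gym groups lie within centres, so this term also absorbs their contribution to the variance of the difference.

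In section 2.15, state that the 80% power assumes independent patients, and give the power over a range of ICCs, for example 0.02 to 0.10.

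Centre and arm are already recorded, and no extra patients are needed. The cost is a wider interval in the sensitivity analysis (SE about 6% larger at a centre-level ICC of 0.02 and 14% at 0.05), fewer degrees of freedom and a less favourable stated power. The sensitivity analysis is also slightly conservative if the extra variance is truly zero. In a balanced moment-based version of it, the variance was then estimated as zero in only about 54% of runs, and the one-sided error was 1.8%.

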Based on the above considerations, this paper describes the design of a pragmatic trial that will be carried out on a large sample of patients who have experienced a stroke within the six months prior to enrolment. Pragmatic trials aim at evaluating the effectiveness of an intervention in scenarios that mainly reflect clinical practices, in contrast with explanatory trials, whose aim is to evaluate the efficacy, i.e., the capacity to produce a desired effect in expert hands under ideal circumstances [25]. As a matter of fact, while explanatory trials answer the question “Can an intervention work?”, a pragmatic trial focuses on the question “Does the intervention work?” in real-world clinical practice. The goal of the trial is to evaluate the effectiveness and sustainability of a multimodal treatment using robotics and advanced technologies compared to traditional multimodal treatment in the recovery of daily living activities. Specifically, we aim to verify the non-inferiority of the robotic treatment when compared to traditional interventions. We decided that a non-inferiority study was appropriate for the primary outcome since there are no evident reasons so far for a robotic treatment to be superior to one-to-one traditional treatment when the two treatments are administered with the same intensity. However, we are confident that this superiority may emerge, for example, for reasons related to patient engagement and compliance, and in any case, the technology might reduce healthcare costs by allowing a lower therapist-to-patient ratio.

This pragmatic trial is part of Mission 1 on the clinical translation of robotics into rehabilitation under the Fit for Medical Robotics (Fit4MedRob) Initiative, funded by the Ministry of University and Research of Italy.

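### Non-inferiority is tested first in a per-protocol set that excludes treatment interrupters, with no rule that the ITT result must agree and no analysis set named for superiority

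*Protocol article*

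**What the plan says.** Section 2.18 defines two sets. ITT holds all randomised patients. PP removes those found ineligible at baseline and "those who did not receive the full treatment (due to treatment interruption for any reason").

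Section 2.18.1 sets the test by "comparing the lower limit of the CI with the non-inferiority margin of −5 points", using a two-sided 95% interval. It then fixes an order: "the mixed-effects model will initially be applied to the PP population". An ITT analysis of all randomised patients comes next, using a repeated-measures mixed model under MAR, with sensitivity analyses for departures from MAR in one or both arms. The section does not say which set decides, whether both must clear the margin, or what follows if they differ.

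The next step reads: "If non-inferiority is concluded for the primary outcome, superiority can be evaluated without the need for correction for multiple comparisons". No analysis set is named for it. Section 2.1.2 lists superiority as a secondary objective, and section 2.18.2 confines continuous secondary outcomes to ITT. But the variable tested is the primary outcome, so that restriction does not clearly apply.

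**The concern.** Excluding patients for something that happens after randomisation gives up the balance that randomisation provides. If interruption is linked to poor progress and is more common in one arm, the PP contrast favours that arm.

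The design makes such a difference plausible. Patients and clinical investigators are unblinded (2.16). The RADT arm has two physiotherapists for four to six patients (2.9.1), while control treatment is one-to-one (2.9.2). Investigators may also remove participants whom they judge no longer to benefit (2.17), and they know the arm when they do so.

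As the text stands, a PP pass with an ITT fail could be reported as non-inferiority and could open the superiority test. A completers-first answer also sits awkwardly with the Introduction, where "a pragmatic trial focuses on the question “Does the intervention work?” in real-world clinical practice".

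**Working it through.** **Inputs from the article.** Margin 5 points, SD 20, power 80%, 15% dropout, 506 evaluable and 596 in total (2.15); one-sided 2.5% from a two-sided 95% interval (2.18.1); 1:1 allocation (2.2), hence 298 per arm. A true difference of 0 is not stated, but it reproduces the planned size.

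**The plan's own figure.** A t-based calculation gives power 0.7998 at 252 per arm and 0.8014 at 253. So 253 per arm, 506 in total, is right, and 506 / 0.85 = 595.3, rounded up to 596. The 15% allowance is about 90 patients. The sample size is not in question.

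**Assumptions (not in the article).** Non-completion rates p_E (RADT) and p_C (control), and a deficit g, the number of points by which non-completers improve less than completers. The true difference among all randomised patients is -5, so any claim of non-inferiority is false.

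**Formulas**
- Bias of the PP contrast: b = (p_E − p_C) × g
- Standard error: SE = 20 × √[1/(298(1 − p_E)) + 1/(298(1 − p_C))]
- False non-inferiority on PP alone: Φ(b/SE − 1.96)

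**Example, 20% RADT and 10% control, g = 10.** b = 0.10 × 10 = 1.0. SE = 20 × √(1/238.4 + 1/268.2) = 1.78. Φ(0.562 − 1.960) = Φ(−1.398) = 8.1%.

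| RADT / control non-completion | g | Bias (points) | False non-inferiority, PP alone |
|---|---|---|---|
| 10% / 20% | 10 | −1.0 | 0.6% |
| 15% / 15% | 10 | 0 | 2.5% |
| 20% / 10% | 5 | +0.5 | 4.7% |
| 20% / 10% | 10 | +1.0 | 8.1% |
| 20% / 10% | 15 | +1.5 | 13.2% |
| 25% / 10% | 10 | +1.5 | 12.9% |

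Simulation agrees to within sampling error: about 0.5%, 2.5% to 2.7%, 8% and 13% for the four rows with g = 10. Equal rates do not guarantee safety. With 15% in each arm but a 10-point deficit only among RADT non-completers, b = 0.15 × 10 = 1.5 and the error is about 13%.

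**Requiring both sets.** In simulation with outcomes observed for everyone, false non-inferiority is about 2.4% at 20% / 10% with g = 10, and about 2.4% in the equal-rates case with the deficit in the RADT arm only. A rule that needs both sets cannot exceed the error of the ITT test alone, which is nominally 2.5%.

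**Power cost.** At a true difference of 0 with 15% loss unrelated to outcome, power is 80.2% for PP alone and 78.7% when both must pass, a loss of 1.5 points.

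**The case against.** **PP is a usual set in a non-inferiority trial**, because ITT can dilute a real difference. This stands. The point concerns how the two sets combine, not the use of PP.

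**The article is a condensed account.** The order of analyses is not a decision rule, and a fuller document may hold one. This stands in part: the text does not say that PP alone decides. But it fixes the margin, the significance level, the order of the sets and the gate to superiority, and leaves out the one condition that would link them.

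**Bias is not shown.** This stands. There are no rates by arm, section 2.11 expects high adherence, and both arms have the same number and length of sessions. If loss is unrelated to outcome, or equal in rate and deficit, PP holds its nominal level. If more is lost from control, PP is conservative.

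**Safeguards exist.** Assessors and data analysis are blinded (2.16). Outcomes are to be collected after interruption, and departures from MAR are examined (2.18.1). These help, but they are given no part in the decision.

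Two stronger readings are tempting. A reader might infer that superiority will be tested in PP. The article names no set, and its rule for secondary outcomes makes ITT at least as natural a reading. A reader might also infer that PP power falls well below 80%. That needs exclusions above the planned 15%, for which the article gives no basis.

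**Conclusion.** The point holds as a gap in the decision rule for the primary claim. The PP analysis leads, ITT has no stated weight, and the set for superiority is open. The article does not show that the PP result will be biased.

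Under the assumed rates with a 10-point deficit, false non-inferiority on PP alone runs from about 0.5% to about 13%, against a nominal 2.5%. The direction depends on which arm loses more poor responders. Were superiority tested in PP, the same bias would carry over at a true difference of 0.

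The protection from requiring both sets depends on obtaining outcomes after interruption. Section 2.18.1 assumes this, but section 2.17 ends data collection on withdrawal from the study and lets patients ask for deletion of their data. The ITT check may therefore be incomplete too. This is a cheap improvement, best made before any results by arm are seen, because choosing between discordant sets afterwards would be post hoc.

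**What to change.** Add to section 2.18.1:

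> Non-inferiority is concluded only if the lower 95% limit exceeds -5 in both the ITT and the PP analysis; superiority is then tested in the ITT population.

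If a fuller protocol or the SAP already contains such a rule, the remaining step is to confirm that it matches.

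The cost is one sentence and a slightly stricter criterion: joint power of about 78.7% instead of 80.2% for PP alone at 15% uninformative loss. No patients need to be added.
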